The main aim is to study the short- and long-term effects of a PNE tool as a supplement to a multimodal rehabilitation (MR) program in BC patients with persistent pain upon finishing adjuvant treatment to determine its impact on pain, physical function and quality of life. Our hypothesis is that a PNE tool as a supplement to a MR program based on exercise and manual therapy techniques, will be more effective in improving persistent pain in cancer patients than an MR program combined with TBI. This will be compared to a control group.

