### Calculation of the sample size

The estimation of the sample size and statistical power for the trial were determined based on the main variable, pain measured through the VAS. Based on a previous study [26] and estimating that patients in the intervention group would have a difference of 15 mm or more in the VAS compared to the control group, differences of at least 5% can be detected with a statistical power of 90% and a significance level alpha α of 0.05. This will require a sample of 24 patients per group, which will result in a total of 72 participants. Therefore, a maximum monitoring loss of 20% will be allowed. To carry out this sample calculation, the G*Power v. 3.1 Software was used.

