### Data analysis

To analyze the results, the statistical program IBM SPSS 26 (IBM Corp., Armonk, NY, USA.) will be used. The descriptive statistics for this study (95% confidence intervals) will use mean and standard deviation (continuous data) or frequencies and percentages (categorical data). The Kolmogorov-Smirnov test will be applied to verify the normal distribution of the variables (p> 0.05). Receiver operating characteristic (ROC) curves will be included to determine the accuracy of the tests. A t test will be used to analyze parametric variables, and a Mann–Whitney U test will be used for nonparametric variables. From the point of view of inferential statistics and to respond to the main objective of this study, an intention-to-treat analysis will be carried out. A 3x3 repeated-measures ANOVA model will be performed using time (baseline, postintervention, follow-up) as a within-subject factor and intervention (first arm, second arm, control) as a between-subjects factor. The Bonferroni test will be used for post hoc analysis. For the study on subgroups with possible differential results, cancer location, type of treatment, elevated tumor stages, age, sex will be used as possible confounding variables in a subsequent multiple regression analysis. A significance level of p value less than 0.05 (P < .05) will be considered. The intergroup effect sizes will be calculated to provide magnitude changes; the effect size will be estimated using Cohen’s d (0–0.19, negligible; 0.20–0.49, small; 0.50–0.79, moderate; ≥0.8, large).

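### Bonferroni is valid for the three arm comparisons but needlessly conservative: at one endpoint and time point, a Shaffer step-down keeps the same 5% bound and has more power

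*Protocol article*

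**What the plan says.** The Data analysis section plans a 3x3 repeated-measures ANOVA with time within subjects and "intervention (first arm, second arm, control) as a between-subjects factor". It then fixes the follow-up procedure: "The Bonferroni test will be used for post hoc analysis". The general threshold is set by "A significance level of p value less than 0.05 (P < .05) will be considered".

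The Introduction states as the hypothesis that PNE added to the MR program "will be more effective in improving persistent pain in cancer patients than an MR program combined with TBI", with the control group as a further comparison.

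The sample size section plans by "estimating that patients in the intervention group would have a difference of 15 mm or more in the VAS compared to the control group", "with a statistical power of 90% and a significance level alpha α of 0.05". It concludes: "This will require a sample of 24 patients per group, which will result in a total of 72 participants". It adds that "a maximum monitoring loss of 20% will be allowed". It gives no SD and no separate planning difference for PNE+MR versus TBI+MR.

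The article does not spell out which comparisons the post hoc analysis covers. The three between-arm comparisons are the natural reading of a model with a three-level arm factor.

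**The concern.** Bonferroni holds every pair to 0.0167 whatever the other pairs show. With exactly three arms this is stricter than familywise control at 5% requires. If one of the three pairwise equalities is false, the other two cannot both be true, because two equalities among three means imply the third. Once one pair has been declared different, at most one true null is left, and the remaining pairs can be tested at the full 0.05.

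What is at stake is power, not validity. The stated hypothesis compares two arms that share the same exercise and manual therapy, so their gap may well be smaller than the gap to control. In a trial of 72 patients, judging that contrast at 0.0167 throughout could turn a real PNE effect into a non-significant result that a different, equally valid rule would have detected.

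**Working it through.** **Inputs from the article.** Three arms, 24 per arm, alpha 0.05 (taken as two-sided, since sidedness is not stated), power 90%, planning difference 15 mm, losses up to 20% (24 × 0.8 ≈ 19 per arm).

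**Assumption.** The SD of the VAS is not given. It is back-solved from the plan's own figure. For a two-sample t test with n = 24 per arm, df = 46, critical value 2.013 and noncentrality d × √(n/2), power of 90% requires d = 0.956, so SD = 15/0.956 = 15.7 mm. The stated 24 per group is reproduced only in this sense and cannot be confirmed. SDs from 12 to 25 mm are therefore examined as well.

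**The two rules.**
- Bonferroni: reject a pair if p < 0.05/3 = 0.0167.
- Shaffer, three arms: if the smallest p < 0.0167, reject that pair and test the other two at 0.05; otherwise stop.

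The first step is identical, and later steps use a higher threshold, so Shaffer can never lose a Bonferroni rejection.

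**Simulation.** Three normal means, pooled variance, one endpoint and one time point, 200,000 runs per scenario. Means are mm of improvement for control / TBI+MR / PNE+MR.

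| Means (mm) | SD | n per arm | PNE+MR vs TBI+MR: Bonferroni → Shaffer | Gain (points) | Gain for TBI+MR vs control (points) |
|---|---|---|---|---|---|
| 0/10/20 | 15.7 | 24 | 41% → 58% | 17.6 | 17.4 |
| 0/7.5/20 | 15.7 | 24 | 62% → 77% | 15.3 | 15.2 |
| 0/7.5/15 | 15.7 | 24 | 22% → 36% | 13.8 | 13.7 |
| 0/10/15 | 15.7 | 24 | 9% → 19% | 9.3 | 15.0 |
| 0/12/15 | 15.7 | 24 | 4% → 10% | 5.6 | 12.5 |
| 0/10/20 | 15.7 | 19 | 32% → 48% | about 16 | not tabulated |

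**Hand check.** The standard error of a pairwise difference is 15.7 × √(2/24) = 4.53 mm. With 69 df the critical values are about 2.45 at 0.0167 and 2.00 at 0.05. For a 10 mm gap, 10/4.53 = 2.21, so power is roughly P(Z > 0.24) ≈ 40% and P(Z > −0.21) ≈ 58%. For a 5 mm gap, 5/4.53 = 1.10, giving roughly P(Z > 1.35) ≈ 9% and P(Z > 0.90) ≈ 18%. These agree with the simulation to within about a point.

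**Sensitivity to the SD (24 per arm).** At 0/10/20 mm, power for the hypothesis contrast moves from 67% to 81% at SD 12, from 24% to 39% at SD 20, and from 15% to 25% at SD 25. At 0/10/15 mm the gain is about 13 points at SD 12 and about 4 at SD 25.

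**Familywise error (24 per arm, one time point).**
- All three arms equal: about 4.3 to 4.4% under both rules.
- The two MR arms equal and control far away: 1.7% with Bonferroni, 5.0% with Shaffer.

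**Two time points.** The design has a post-intervention and a 6-month assessment. If the step-down were applied at full alpha at each, with MR effective and PNE adding nothing, a false PNE claim at one or the other would occur in about 9% of trials, against about 3% with three-pair Bonferroni at each (correlation of 0.5 between times assumed). The 5% bound therefore holds only for a family defined at one endpoint and time point.

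**The case against.** The strongest case for leaving the sentence alone is that Bonferroni is valid, conventional, prespecified, and gives simultaneous intervals that agree with its decisions. All of that stands. A reader might infer that the plan contains a statistical error; it does not.

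Three further inferences are tempting and not supported:

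- **That PNE+MR versus TBI+MR gains most.** This depends on the means, about which the article says nothing beyond 15 mm against control. In the first three patterns tabulated, the gain is the same for TBI+MR versus control. When the PNE increment is the smaller step, TBI+MR versus control gains more (15.0 against 9.3 points at 0/10/15 mm).
- **That Bonferroni's strictness buys nothing.** Its actual error is lower, 1.7% against 5.0%, exactly when MR works and PNE adds nothing. The step-down uses up error that the 5% bound allows. That is a legitimate trade, but not a free gain.
- **That the change rescues the hypothesis test.** At 0/10/15 mm, power is still only 19%.

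Two other objections stand and shape the fix. The family has to name its time point, because using the step-down at both assessments without splitting alpha breaks the 5% bound. And the rule must be applied by hand to unadjusted p-values. The remaining objection, that a fuller analysis plan may refine the procedure, does not remove the point: the article does not leave the method open but names Bonferroni.

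**Conclusion.** The point holds as a cheap improvement. For three arms at one endpoint and time point, the Shaffer step-down keeps the familywise error within the same 5% bound as Bonferroni, rejects everything Bonferroni rejects, and has more power for every pair. Across the patterns examined at SD 15.7 mm and 24 per arm, the hypothesis contrast gains about 6 to 18 percentage points.

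The logical part (validity, and never rejecting less) needs no assumption about the SD. The size of the gain rests on an SD that the article does not state, on normal data with common variance, on two-sided testing, and on assumed patterns of means. The gain shrinks as the SD grows or as the PNE increment gets smaller.

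**What to change.** In the Data analysis section, replace the Bonferroni sentence with:

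> For the primary outcome (VAS) at one prespecified primary time point, the three pairwise comparisons between arms will be tested by the Shaffer step-down procedure: the smallest p-value against 0.0167 and, if significant, the other two against 0.05; comparisons at the other time point are secondary.

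The sponsor should name the time point in that sentence. If both time points are to support a claim, split alpha between them: 0.025 each, so 0.025/3 = 0.0083 for the smallest p-value and then 0.025 for the other two. The total stays within 0.025 + 0.025 = 0.05.

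Keep Bonferroni simultaneous confidence intervals for reporting.

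Cost: one sentence, written before anyone sees outcomes by arm, and no additional patients or data. SPSS supplies unadjusted pairwise p-values and the rule is applied by hand. The small downside is that the Bonferroni intervals may not match the step-down decisions exactly: a pair can be declared different while its interval still includes zero. The report should say so.

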**Methods:**

An 8-week double-blinded randomized controlled trial will be conducted, including 72 participants who had BC and who have persistent pain, randomized into three groups: PNE program + MR program, traditional biomedical information + MR program and control group. The PNE program will include educational content that participants will learn through a mobile app and the MR program will include a concurrent exercise program and manual therapy. The primary outcome will be the perceived pain assessed using the Visual Analogue Scale and secondary outcomes are others related to pain, physical function and quality of life. All outcomes will be evaluated at baseline, at the end of the intervention and 6 months after the end of intervention.

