**Fig 2 pone.0290096.g002:**
[figure not shown]
Overview of the study.

The inclusion and exclusion criteria for eligible participants of the study are detailed in Table 1.

**Table 1 pone.0290096.t001:** Inclusion/Exclusion criteria.

Inclusion criteria	Exclusion criteria
a) Survivors of BC cancer [25]	a) Physical or mental impossibility of carrying out the tests of the study
b) Aged 18 years or older	b) Have suffered chronic pain in the orofacial, cranial, cervical, brachial and shoulder areas or trauma to these regions prior to the cancer diagnosis
c) Have undergone surgery and/or have finished adjuvant treatment (radiotherapy and/or chemotherapy) at least 6 months up to 2 years ago	c)Participating in other physical recovery programs during the interventions
d) Have no active cancer	
d) Have pain ≥ 4 (VAS 0 to 10) in regions related to the tumor area (orofacial, cranial, cervical, brachial and shoulder) for more than 3 months. e) Pain can be compatible with one or more of these conditions: central sensitization, neuropathy, peripheral pain and pain from surgery	

BC = Breast cancer; VAS = Visual analogue scale.

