### Randomization and blinding

Upon completion of the recruitment process, participants will be randomized (ratio 1:1) into each of the groups using a random number generation program (EPIDAT 4.2, Xunta de Galicia, Spain). Assessors and data analyzers will be blinded to the randomization of the participants. The blinding of assessors will be guaranteed by the fact that some members of the research group will perform first assessments and others will perform the post-treatment and follow-up assessments.

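### The subgroup analysis is described as confounder adjustment with no arm-by-factor interaction, so as described it does not test for differential effects; two of its five factors suit a breast-cancer-only trial poorly

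*Protocol article*

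**What the plan says.** In the protocol article, the Data analysis section sets the purpose with the words "For the study on subgroups with possible differential results". The same sentence then gives the method: "cancer location, type of treatment, elevated tumor stages, age, sex will be used as possible confounding variables in a subsequent multiple regression analysis". No interaction term is mentioned. The main analysis just before it is a 3x3 repeated-measures ANOVA with time and arm as its only factors. The section sets a 0.05 significance level and does not mark the subgroup work as exploratory.

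On the population, Table 1 requires "Survivors of BC cancer", and the abstract describes the trial as "including 72 participants who had BC and who have persistent pain, randomized into three groups". Table 1 admits adults ("b) Aged 18 years or older") and has no criterion on sex. The share of men expected is not given anywhere.

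On allocation, the Randomization and blinding section says that "participants will be randomized (ratio 1:1) into each of the groups".

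**The concern.** Whether results differ between subgroups is a question of effect modification: does the arm effect change with the level of a factor? Adjusting for a confounder answers another question, namely what the single arm effect is once the factor is held fixed. The sentence states the first aim and assigns the factors the role that belongs to the second. Random allocation also means that baseline factors do not systematically confound the arm comparison, so the label does not describe what the analysis needs to do.

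An analyst who follows the text would obtain a coefficient for, say, tumour stage and could report it as a differential result at the 0.05 level, although it shows only that stage is related to pain. Two factors raise a further problem: cancer location may not vary at all in this population, and sex may vary too little to be useful.

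**Working it through.** **1. What the described model estimates.** Take two arms of 24 and a binary factor X split 12/12 in each arm. Suppose the true arm effect on the VAS is 0 mm when X = 0 and -30 mm when X = 1, with no effect of X in the comparison arm.

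- Main-effects model, y = a + b·arm + c·X. With this balance, b is the average of the two subgroup effects: (0 + (-30))/2 = -15 mm. Likewise c is the average of the X difference in the two arms: (0 + (-30))/2 = -15 mm.
- A least-squares simulation (4,000 runs, residual SD 15.68 mm) returned means of -15.0 mm for b and -15.1 mm for c. One subgroup gains nothing and the other gains 30 mm, but the output shows a uniform arm effect and an apparent factor effect.
- Adding d·arm·X recovered 0.0 mm for the arm effect at X = 0 and -29.9 mm for the interaction. Only this term addresses the stated aim.

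**2. Cancer location.** If it means tumour site, its column is constant and proportional to the intercept. A design matrix with intercept, arm and a constant column has rank 2 out of 3, so the coefficient cannot be estimated.

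**3. Sex.** The share of men is an assumption, taken over a range. Expected men = 72·p; chance of at least one man in every arm = (1 - (1 - p)^24)^3.

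| Assumed share p | Men expected in 72 | Chance of at least one man in every arm |
|---|---|---|
| 0.5% | 0.4 | 0.1% |
| 1% | 0.7 | 1% |
| 2% | 1.4 | 6% |
| 5% | 3.6 | 35% |

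**4. Illustration of precision with an interaction term.** The Calculation of the sample size section gives 24 per group, 90% power, alpha 0.05 and "a difference of 15 mm or more in the VAS compared to the control group". It states no SD, so the 24 cannot be reproduced. Solving backwards with a two-sided t test, the detectable standardised difference is 0.956, so SD = 15/0.956 = about 15.7 mm. Other readings give 17.5 mm (one-sided) or about 13.9 to 14.3 mm (if 24 already includes 20% loss, leaving 19 to 20 evaluable).

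With SD 15.68 mm:

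- SE of the arm difference = 15.68·√(2/24) = 4.53 mm.
- SE of the interaction at a 50:50 split = 15.68·√(2/12 + 2/12) = 9.05 mm, twice as large. The ratio is 15/9.05 = 1.66.

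Two-sided noncentral-t power for a 15 mm interaction in a two-arm contrast:

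| Per arm | Factor split | Power | Interaction detectable at 90% power |
|---|---|---|---|
| 24 | 50:50 | 37% | 30 mm |
| 20 | 50:50 | 31% | 33 mm |
| 24 | 25:75 | 29% | 35 mm |
| 20 | 25:75 | 25% | 38 mm |

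**The case against.** The strongest reply is that a multiple regression can carry interaction terms, that the article writes out no model equation, and that the terms of a secondary model are commonly left to a fuller document. This stands in part. A reader might infer that the analysis is incapable of showing differential effects, or that the subgroup question will certainly be answered wrongly; the text does not go that far, because it does not exclude interactions. The reply does not remove the point, however. The article assigns the factors a role, and that role is adjustment, which does not match the aim given in the same sentence. This is a mismatch in what is stated, and an analysis plan that followed the sentence would inherit it.

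Other parts of the reply also stand:

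- Location is undefined. It could mean side or quadrant of the breast, in which case it varies. A flat statement that it is constant goes beyond the document.
- The documents do not say that sex is nearly constant. That rests on the assumed range above.
- The power figures do not measure the defect. They describe a replacement test and depend on a back-solved SD, an assumed split, two of the three arms, and an interaction as large as the whole planned effect.
- With 24 per arm, chance imbalance is plausible, and adjusting for prognostic factors is a legitimate secondary analysis. It is simply not a subgroup analysis.

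**Conclusion.** The point holds in a limited form. The stated aim is effect modification, the stated method is confounder adjustment, and no arm-by-factor interaction is named. Followed as written, the regression gives one common arm effect and a set of prognostic coefficients, and so does not test whether the effect differs by subgroup.

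Two additions are conditional. Cancer location is inestimable if it means tumour site. Sex cannot support a subgroup if men make up 0.5% to 5% of participants, which is about 0.4 to 3.6 of 72.

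Power for a 15 mm interaction is illustrative only: about 37% in the most favourable case examined, about 29% to 31% with either an uneven split or 20% loss, and about 25% with both. These figures justify an exploratory label and nothing more.

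A reader might infer that the trial's main result is compromised. It is not: this is a secondary analysis, and the primary arm comparison and the sample size are untouched. The correction is worth making but is modest.

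**What to change.** Replace the subgroup sentence in the Data analysis section with wording to this effect: exploratory analyses will examine whether the arm effect on VAS pain differs by age, type of treatment and tumour stage; each factor will be examined one at a time by adding it and its interaction with arm to the model (arm by time by factor, if kept within the repeated-measures ANOVA); interaction estimates will be reported with 95% confidence intervals and labelled exploratory.

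Define cancer location as something that varies in this population, for example side, or drop it. Drop sex as a subgroup factor.

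If prognostic adjustment was what the authors meant, say so, list those covariates for that purpose, and do not present the result as a subgroup analysis.

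The cost is wording only: no further data, visits or participants are needed.

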## Discussion

The current trial will determine if the application of combined PNE with an MR program presents higher efficacy in reducing pain than the application of this MR program without PNE. Previous studies have demonstrated that the combination of PNE with other therapies such as exercise or dry needling, obtains better results in kinesiophobia and pain than the sum of its parts in chronic neck pain [65, 66]. These findings in PNE are consistent with the results obtained in chronic low back pain and other chronic musculoskeletal pain conditions, in conjunction with usual physiotherapy interventions and exercise, respectively [67, 68]. However, despite these benefits, to our knowledge no intervention has tested the effects of a PNE app within a physical therapy program in a breast cancer population suffering from pain and dysfunction. Furthermore, earlier evidence shows that more research is needed to observe the effects of pain management and healthy lifestyle interventions in cancer survivors [69].

Different studies have shown the efficacy of MR programs (exercise, kinesitherapy and/or manual therapy) in health issues related to pain and dysfunction associated with medical treatment of BC [70–72] or colon cancer [73]. We therefore consider it possible that similar results could be achieved with MR programs in patients who had breast cancer and present with persistent pain. A recent study has piloted the effectiveness of a PNE session in cancer survivors, and they present preliminary but promising results [19]. It seems necessary to design and implement appropriate treatment programs for this specific population. Currently, the cancer population still faces difficulties in receiving optimal treatment programs for their illness or survivorship heaviness and support to maintain a healthy lifestyle [69].

Although participants can also have different levels of PA outside the program. It will be registered with the IPAQ-SF questionnaire and considered for analyses. Even though low adherence levels might be expected from the exercise program, supervision by the physical therapist and social interaction between participants will reinforce adherence and physical function. This could open up the possibility to participants to share their pain coping strategies and all achievements made. In addition, despite there will be participants who will not know how to use the app, they will be taught how to properly use it to benefit the most from PNE.

The proposed study may help BC patients with persistent pain improve their pain experience, quality of life and provide for more adaptive pain-coping strategies. This protocol could propose an action guide to implement different integral approaches for the treatment of sequelae. If the group that includes PNE sessions proves to be more effective in reducing pain and improving physical function and quality of life than the groups without PNE, this treatment option could be offered to this patient profile and it could be easily implemented in the healthcare systems due to its low costs. Our results will be disseminated through social media, professional conferences and international refereed journals.

We expect moderate effectiveness on pain, physical function and quality of life due to the multimodal approach and the fact that we give the PNE contents 6 months after having undergone surgery and/or have finished adjuvant treatment (radiotherapy and/or chemotherapy). Providing PNE in the early postoperative stage [21], could be a barrier in the process of reconceptualizing pain as having psychological distress and poor cognitive functions (attention and memory) are common in that period [74–76].

Results from the PaiNEd trial will be disseminated in peer-reviewed journals, national and international conferences focused on pain, oncology and rehabilitation. Furthermore, findings will also be available through social media of the research team. Finally, participants and other interested cancer patients will know the final results of the study.
